#### **7.1.2 Exclusion Criteria**

1. Patients with any condition which, in the opinion of the Investigator, makes the patient unsuitable for inclusion based on clinical judgment.
2. Labeled contraindications of betahistine dihydrochloride (Betaserc®) treatment.
3. Patients with middle or inner ear infection.
4. Patient with psychiatric disorders, significant neurological disorder or spinal cord damage.

[figure not shown]

5. Patients receiving any other agents for peripheral vestibular vertigo such as diuretics, transtympanic gentamycin, cinnarizine, competitive antagonist of histamine, blocking H1-histamine receptors.
6. Patients undergoing ear surgery for vestibular disorders.
7. Female patients who are pregnant, planning to become pregnant or are breast-feeding.
8. Inability to comply with the protocol requirements.
9. Participation in any other clinical trial within last 30 days.
10. Patients who had previous betahistine therapy within 4 weeks of start of current betahistine dihydrochloride (Betaserc®) treatment course.

## **7.2 Number of Patients to be Enrolled**

A total of 310 patients will be enrolled in this program from approximately 10-35 centers in Russia and Ukraine.

## **7.3 Investigator Selection Criteria**

Criteria that will be used to select investigators to participate in the program:

- 1) Specialized in otorhinolaryngologists (ENT specialists) or neurologists
- 2) Ability to appropriately conduct the observational program
- 3) Availability of the outpatient population with vestibular vertigo

## **7.4 Program Duration**

Each patient will be observed approximately 2 months within the observational treatment period and approximately 2 months within follow-up period for the evaluation during the course of vestibular vertigo after Betaserc® treatment discontinuation. Based on underlying ICD-10 diagnosis and the clinical judgment of the physician, duration of treatment period

[figure not shown]

can be less than 2 months or can continue after termination of program's observational treatment period. However, only patients who finish betahistine dihydrochloride (Betaserc®) within 1 - 2 months of therapeutic period will be observed for the assessment of the course of vestibular vertigo within 2 months of follow-up period.

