7. Overall clinical response assessed by patient will be determined based on a four-point-scale, where 4 = excellent, 3 = good, 2 = fair, and 1 = poor. Proportion of patients in each category at the end of observational treatment period will be determined in patients who completed betahistine treatment over a period less or equal 30 days and in patients who completed betahistine treatment over a period more than 30 days but less or equal 60 days. Proportion of patients in each category at Visit 2 will be determined in patients who completed betahistine treatment over a period more than 30 days but less or equal 60 days.
8. Clinical response as improvement of vertigo associated symptoms (tinnitus, hearing loss, nausea, vomiting, faintness and headache) and evaluated by physician will be determined based on a four-point-scale, where 4 = excellent, 3 = good, 2 = fair, and 1 = poor. Proportion of patients in each category at the end of observational treatment period will be determined in patients who completed betahistine treatment over a period less or equal 30 days and in patients who completed betahistine treatment over a period more

[figure not shown]

than 30 days but less or equal 60 days. Proportion of patients in each category at Visit 2 will be determined in patients who completed betahistine treatment over a period more than 30 days but less or equal 60 days.

9. Clinical response as improvement of vertigo associated symptoms (tinnitus, hearing loss, nausea, vomiting, faintness and headache) and evaluated by patient will be determined based on a four-point-scale, where 4 = excellent, 3 = good, 2 = fair, and 1 = poor. Proportion of patients in each category at the end of observational treatment period will be determined in patients who completed betahistine treatment over a period less or equal 30 days and in patients who completed betahistine treatment over a period more than 30 days but less or equal 60 days. Proportion of patients in each category at Visit 2 will be determined in patients who completed betahistine treatment over a period more than 30 days but less or equal 60 days.

10. Change of vestibular vertigo attacks frequency from the end of observational treatment period to the end of 1st month of follow-up period in patients who completed betahistine treatment over a period less or equal 30 days and in patients who completed betahistine treatment over a period more than 30 days but less or equal 60 days.

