11. Change of vestibular vertigo attacks frequency from the end of observational treatment period to the end of 2nd month of follow-up period (end of follow-up period) in patients who completed betahistine treatment over a period less or equal 30 days and in patients who completed betahistine treatment over a period more than 30 days but less or equal 60 days.

12. Specific underlying ICD-10 diagnosis account for Vestibular Vertigo. Proportion of patients in each category at Visit 1 will be determined in total study population.

[figure not shown]

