### *II. Evaluation of the course of vestibular vertigo in post-treatment period, follow-up period (only for patients who finished betahistine dihydrochloride (Betaserc®) 1 - 2 months treatment period)*

**Visit 4:** 30th day from the last dose of Betaserc®

**Visit 5:** 60th day from the last dose of Betaserc®, End of follow-up period

In the post-treatment period, the site personnel will contact the patients personally or by phone on 30 days after the last dose of Betaserc® to assess any SAE that may have started after the end of therapeutic observational period and also to follow-up on any SAE that were continuing from the time of last contact with patient.

[figure not shown]

Figure 2 below presents a schematic of the program plan and Table 2 below summarizes the various activities to be conducted at each of these visits.

[figure not shown]

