| Overall clinical response and clinical response as improvement of vestibular vertigo associated symptoms based on four-point scales  |                        | X                                                                                 | X                                                                                 |                                                                    |                                                           |
| SAE monitoring                                                                                                                       | X                      | X                                                                                 | X                                                                                 | X                                                                  |                                                           |

 This program does not include patients who required betahistine therapy, according to physician's decision, more than 60 days.

 Actual date of visit may be up to 7 days from the last betahistine dose, otherwise proceed to Visit 4.

[figure not shown]

 This coincides with Visit 2 in case patient had completed betahistine treatment period lasting 30 days or less. In case physician decides to continue betahistine therapy beyond 30 days, Visit 3 will be a separate visit from Visit 2.

 For patients whom physician decides to continue betahistine therapy beyond 60 days treatment course, no follow up will be done and end of observational treatment period will denote end of program.

 Includes sex, age, race (white, black, asian, other), weight and height

 Heart rate, blood pressure (systolic and diastolic)

 for more detailed information about Scale for Vestibular Vertigo Severity Level and Clinical Response Evaluation please see section 6.3, Figure 1 and Table 1.

 Four-point-scale, where 4 = excellent, 3 = good, 2 = fair, and 1 = poor.

 30 days after end of program treatment or early termination, a telephone call will be made to enquire about development of any SAE. If there is a positive feedback, relevant medical history and adverse event details will be collected.

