7. Overall clinical response assessed by patients based on a four-point scale will be presented with number and proportion of subjects in each category at the end of observational treatment period for patients who completed betahistine treatment over a period less or equal 30 days and at Visit 2 and 3 for patients who completed betahistine treatment over a period more than 30 days but less or equal 60 days.
8. Clinical response as improvement of vertigo associated symptoms (tinnitus, hearing loss, nausea, vomiting, faintness and headache) and evaluated by physicians based on a four-point scale will be presented with number and proportion of patients in each category at the end of observational treatment period for patients who completed betahistine treatment over a period less or equal 30 days and at Visit 2 and 3 for patients who completed betahistine treatment over a period more than 30 days but less or equal 60 days.
9. Clinical response as improvement of vertigo associated symptoms (tinnitus, hearing loss, nausea, vomiting, faintness and headache) and evaluated by patients based on a four-point scale will be presented with number and proportion of subjects in each category at the end of observational treatment period for patients who completed betahistine treatment over a period less or equal 30 days and at Visit 2 and 3 for patients who completed betahistine treatment over a period more than 30 days but less or equal 60 days.
10. Change of vestibular vertigo attacks frequency in number of monthly attacks from the end of observational treatment period to 1st month of follow-up and from the end of observational treatment period to 2nd month of follow-up will be presented for patients who completed betahistine treatment over a period less or equal 30 days and for patients who completed betahistine treatment over a period more than 30 days but less or equal 60 days and will be summarized with number of patients, mean, standard deviation, median, 1st quartile, 3rd quartile, minimum and maximum values. Descriptive statistics will be
-

[figure not shown]

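### Sections 7.4 and 7.5 limit post-treatment follow-up to 1 to 2 month courses, while Table 2 sets no minimum and secondary endpoints 10 and 11 need follow-up data after courses of 30 days or less

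*Protocol*

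**What the plan says.** **Who is followed, according to the text.** Protocol section 7.4 (Program Duration) first allows treatment to be shorter than two months or to run past the observational treatment period. It then says that "only patients who finish betahistine dihydrochloride (Betaserc®) within 1 - 2 months of therapeutic period will be observed" after stopping. Section 7.5, part II, which introduces Visits 4 and 5, labels the follow-up period as "only for patients who finished betahistine dihydrochloride (Betaserc®) 1 - 2 months treatment period".

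**Who is followed, according to Table 2.** Footnote 3, on the end-of-treatment visit, provides for short courses: "This coincides with Visit 2 in case patient had completed betahistine treatment period lasting 30 days or less". Footnote 2 sends patients on to Visit 4 if the earlier visit window is missed and names no minimum duration. Footnote 4 withholds follow-up only from patients whose therapy continues beyond 60 days.

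**What must be reported.** In section 6.4, item 10 asks for the change in attack frequency from the end of treatment to the end of the first "month of follow-up period in patients who completed betahistine treatment over a period less or equal 30 days", and likewise in those treated for more than 30 and up to 60 days. Item 11 asks the same for the second month, in the same two strata. Item 10 of the secondary-endpoint analysis in section 11.0 carries both strata forward: the change to the second "month of follow-up will be presented for patients who completed betahistine treatment over a period less or equal 30 days". It adds paired tests.

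**The concern.** One part of the protocol decides who has Visits 4 and 5, and another decides in whom their data are reported. The two do not match. A patient who finishes after 10, 14 or 21 days belongs to the stratum of 30 days or less in endpoints 10 and 11. On a literal reading of sections 7.4 and 7.5, that patient is not followed.

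The course of vertigo after stopping is secondary objective 2 and a stated purpose of the program in section 5.0. If short courses are not followed, that objective is answered only for courses of about a month or longer, and the short stratum describes a narrow selection. Section 7.4 also ties treatment duration to the underlying diagnosis and the physician's judgment. A cut-off on duration may therefore select by diagnosis, and section 11.0 plans an exploratory look at the post-treatment course by diagnosis.

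**Working it through.** **The plan's own figures.** The protocol gives no size for the short-course follow-up stratum. Its only sample size is for the primary proportion, and it reproduces: n = 1.96² × 0.80 × 0.20 / 0.05² = 245.85, rounded up to 246; with 20% dropout, 246 / 0.80 = 307.5, rounded up to 308; 310 are to be enrolled. None of this depends on who attends Visits 4 and 5.

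**Source of the follow-up data.** In Table 2 and section 7.5.2, attack counts after treatment are registered only at Visits 4 and 5. The separate contact 30 days after the last dose (section 7.5, part II; Table 2, footnote 9) asks about serious adverse events only. A patient without Visits 4 and 5 therefore contributes nothing to endpoints 10 and 11.

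**Overlap of the two rules.** Let treatment duration be a whole number of days. The strata in section 6.4 are S1 = days 1 to 30 and S2 = days 31 to 60. Under the literal rule, durations eligible for follow-up are E = day m to day 60, where m is the length of one month. The protocol does not define m, so three values are shown.

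| Length of one month (m) | E ∩ S1 | Durations in S1 without follow-up | E ∩ S2 |
|---|---|---|---|
| 28 days | days 28, 29, 30 | 27 of 30 | all 30 (days 31 to 60) |
| 30 days | day 30 only | 29 of 30 | all 30 |
| 31 days | none | 30 of 30 | all 30 |

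Under the Table 2 footnotes, E = days 1 to 60. E ∩ S1 is then all 30 durations and nothing is lost.

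**Comparisons affected.** Two time points (months 1 and 2 of follow-up) in two strata give 2 × 2 = 4 paired comparisons. The two in S1 are affected; the two in S2 are not.

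**Patients affected.** The protocol gives no distribution of treatment duration, so this cannot be computed. As an assumption for illustration only: suppose 10% to 50% of 246 patients have courses of 30 days or less, that is 0.10 × 246 ≈ 25 to 0.50 × 246 = 123. If 0% to 50% of these stop at about day 30, the S1 follow-up results would rest on between 0 and 0.50 × 123 ≈ 62 patients.

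**The case against.** The best reply is that section 7.4 is loosely worded rather than restrictive. The sentence before the limit mentions both shorter treatment and treatment that goes on past the observational period. The limit could be aimed only at those who go on, with finishing within one to two months meaning finishing by the end of month 1 or month 2. That matches the visit plan (Visit 2 up to day 30, Visit 3 up to day 60), the two strata in section 6.4, and footnotes 2 to 4 of Table 2. On this reading the short stratum is complete.

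This is a fair reading, and it rules out stating as fact that the stratum will be empty. It does not remove the conflict. The label in section 7.5, part II, speaks of a finished course of one to two months, and under the loose reading its lower bound has no function. The current text supports two different rules. Figure 2 might settle which was meant, but it is not available in the text reviewed.

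It can also be said that secondary p-values and intervals are declared descriptive in section 11.0, and that section 5.0 describes the post-treatment assessment as descriptive. That stands, and it limits the severity. A statistical analysis plan cannot repair the problem, however: it can redefine a stratum, but it cannot recover visits that were never made.

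A reader might go further and infer that a large share of patients will lose follow-up, that centers will certainly apply the limit differently, or that those lost are the quick recoveries and the treatment failures. The protocol supports none of these. It gives no share of short courses, says nothing about how centers will interpret the limit, and does not report why patients stop early. The strata are also restricted to patients who completed treatment, so stopping for failure may be recorded as early termination.

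**Conclusion.** The point holds as an internal contradiction with a moderate consequence. Sections 7.4 and 7.5, part II, state a one-month minimum for follow-up; Table 2 states none; and endpoints 10 and 11 need patients below that minimum. If the minimum is applied literally, the stratum of 30 days or less holds no one, or only courses ending on about days 28 to 30. Its two follow-up comparisons then cannot describe what happens after short courses.

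The conclusion rests on the literal reading and on attack counts coming only from Visits 4 and 5. The damage is confined to one stratum of two descriptive secondary endpoints and to the part of secondary objective 2 that they serve. Nothing here casts doubt on the primary endpoint or the planned enrollment.

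**What to change.** Reconcile sections 7.4 and 7.5, part II, with the Table 2 footnotes and with endpoints 10 and 11, and check that Figure 2 shows the same rule. Either route works:

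- **Follow everyone the endpoints need.** In sections 7.4 and 7.5, part II, replace the one to two month condition by a statement that Visits 4 and 5 apply to all patients who finish betahistine within 60 days of the first dose. Table 2 and section 6.4 can then stand. The cost is a short amendment and one or two routine follow-up contacts per short-course patient. These patients already have a contact about serious adverse events 30 days after the last dose, at which the attack count could also be taken.
- **Keep the restriction, if it is intended.** Delete or redefine the stratum of 30 days or less in endpoints 10 and 11 and in item 10 of the section 11.0 analysis, add the minimum to the Table 2 footnotes, and say that secondary objective 2 does not cover shorter courses. This costs no extra visits but gives up the post-treatment description after short courses.

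The first route keeps the endpoints as written and is the better choice if enrollment has not gone far, because missed visits cannot be recovered later.

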## **7.5 Program Conduct**

The patient visits will be scheduled based on routine practice of the physician. 60 days of observational treatment period has been chosen as a length of time sufficient to generate useful effectiveness data. Follow-up visits for this program has been recommended keeping in mind the treating physician's usual pattern of follow-up consultations.

To optimize data collection, three visits are indicated within approximately 2 months of observational treatment period and two visits within approximately 2 months of follow-up period:

### *I. Observational treatment period*

**Visit 1:** Baseline/Start of therapy

**Visit 2:** up to 30th day from the first dose of Betaserc®

**Visit 3:** up to 60th day from the first dose of Betaserc®, End of observation treatment period / Early Termination

### *II. Evaluation of the course of vestibular vertigo in post-treatment period, follow-up period (only for patients who finished betahistine dihydrochloride (Betaserc®) 1 - 2 months treatment period)*

**Visit 4:** 30th day from the last dose of Betaserc®

**Visit 5:** 60th day from the last dose of Betaserc®, End of follow-up period

In the post-treatment period, the site personnel will contact the patients personally or by phone on 30 days after the last dose of Betaserc® to assess any SAE that may have started after the end of therapeutic observational period and also to follow-up on any SAE that were continuing from the time of last contact with patient.

[figure not shown]

Figure 2 below presents a schematic of the program plan and Table 2 below summarizes the various activities to be conducted at each of these visits.

[figure not shown]

**Figure 2: Overall Investigational Plan of Study**

[figure not shown]

[figure not shown]

Table 2 Program Activities

| Weeks of Treatment                                                                                                                               |                        | Observational treatment period                                        |                                                                                   | Evaluation of the course of vestibular vertigo in follow-up period |                                                           |
|--------------------------------------------------------------------------------------------------------------------------------------------------|------------------------|-----------------------------------------------------------------------------------|-----------------------------------------------------------------------------------|--------------------------------------------------------------------|-----------------------------------------------------------|
|                                                                                                                                                  | Visit 1                | Visit 2                                                                           | Visit 3                                                                           | Visit 4                                                            | Visit 5                                                   |
|                                                                                                                                                  |                        | Expected up to 30 th day from the first dose of Betaserc®  | Expected up to 60 th day from the first dose of Betaserc®  | 30 th (±7) day from the last dose of Betaserc®          | 60 th (±7) day from the last dose of Betaserc® |
|                                                                                                                                                  | Screening/
Baseline |                                                                                   | End of observational treatment period  /Early termination           |                                                                    | End of follow-up period                                   |
| Patient Authorization (Consent) for Use/Disclosure of Data                                                                                       | X                      |                                                                                   |                                                                                   |                                                                    |                                                           |
| Inclusion / exclusion criteria                                                                                                                   | X                      |                                                                                   |                                                                                   |                                                                    |                                                           |
| Register date of start of betahistine dihydrochloride (Betaserc®) treatment                                                                      | X                      |                                                                                   |                                                                                   |                                                                    |                                                           |
| Demographics                                                                                                                         | X                      |                                                                                   |                                                                                   |                                                                    |                                                           |
| Medical history                                                                                                                                  | X                      |                                                                                   |                                                                                   |                                                                    |                                                           |
| Concomitant medication                                                                                                                           | X                      | X                                                                                 | X                                                                                 | X                                                                  | X                                                         |
| Physical Exam (including vitals  )                                                                                                   | X                      |                                                                                   |                                                                                   |                                                                    |                                                           |
| Specific underlying ICD-10 diagnosis account for Vestibular Vertigo                                                                              | X                      |                                                                                   |                                                                                   |                                                                    |                                                           |
| Number of monthly vertigo attacks                                                                                                                | X                      | X                                                                                 | X                                                                                 | X                                                                  | X                                                         |
| Scale for Vestibular Vertigo Severity Level and Clinical Response Evaluation                                                         | X                      | X                                                                                 | X                                                                                 |                                                                    |                                                           |
| Overall clinical response and clinical response as improvement of vestibular vertigo associated symptoms based on four-point scales  |                        | X                                                                                 | X                                                                                 |                                                                    |                                                           |
| SAE monitoring                                                                                                                       | X                      | X                                                                                 | X                                                                                 | X                                                                  |                                                           |

 This program does not include patients who required betahistine therapy, according to physician's decision, more than 60 days.

 Actual date of visit may be up to 7 days from the last betahistine dose, otherwise proceed to Visit 4.

[figure not shown]

 This coincides with Visit 2 in case patient had completed betahistine treatment period lasting 30 days or less. In case physician decides to continue betahistine therapy beyond 30 days, Visit 3 will be a separate visit from Visit 2.

 For patients whom physician decides to continue betahistine therapy beyond 60 days treatment course, no follow up will be done and end of observational treatment period will denote end of program.

 Includes sex, age, race (white, black, asian, other), weight and height

 Heart rate, blood pressure (systolic and diastolic)

 for more detailed information about Scale for Vestibular Vertigo Severity Level and Clinical Response Evaluation please see section 6.3, Figure 1 and Table 1.

 Four-point-scale, where 4 = excellent, 3 = good, 2 = fair, and 1 = poor.

 30 days after end of program treatment or early termination, a telephone call will be made to enquire about development of any SAE. If there is a positive feedback, relevant medical history and adverse event details will be collected.

